## Abstract

**Background:**

Stimulation of the primary motor cortex (M1) has been shown to reduce the pain of neuropathy in multiple studies. There are several methods of stimulation both invasive and non-invasive. Recent work by this laboratory has seen that 40% of a sample of chronic neuropathic pain patients responded positively to non-invasive repetitive transcranial magnetic stimulation (rTMS) to the motor cortex with a reduction in pain levels by at least 20%. The effect however is short lived and multiple return visits are necessary to maintain this response. Transcranial direct current stimulation (tDCS) offers a more mobile method of motor cortex stimulation and is similarly non-invasive. The protocol described is designed to assess the analgesic effect of a home-based tDCS treatment device on chronic neuropathic pain in both responders and non-responders to previous TMS treatment.

**Methods/design:**

This article reports the protocol for a randomised, sham-controlled, double-blinded crossover study in which patients with chronic neuropathic pain (*n* = 24) will receive anodal, cathodal and sham tDCS over M1. All patients will have previously completed a study of rTMS of the motor cortex and have been designated as responders or non-responders to this modality.

Patients receive all three tDCS stimulation types by self-administration. We assess the effect on pain scores [numerical rating scale (NRS)], self reported health status (Short Form-36 Health Survey) and anxiety/depression (Hospital Anxiety and Depression Scale). A linear mixed model with fixed effects will analyse changes in pain scores from pre- to post- interventions. Analysis will be carried out on an intention-to-treat basis. A proportion analysis will also be carried out with patients separated into either responders or non-responders to previous TMS.

Safety will be assessed throughout the study by monitoring of adverse events.

**Discussion:**

The result of this trial will assess the efficacy of self-administered tDCS of the motor cortex in the treatment of chronic neuropathic pain and also provide insight into whether a potential differential effect is seen in patients that have previously been shown to be either responsive or non-responsive to rTMS over the same area.

**Trial registration:**

ISRCTN56839387 date 27 January 2014. First patient randomised to trial 30 October 2012.

## Background

Stimulation of the primary motor cortex (M1) of the brain was first shown to reduce central pain in patients by Tsubokawa et al. [1] using implanted electrodes in the epidural space around the brain. More recently, non-invasive methods of cortical stimulation have been tested such as repetitive transcranial magnetic stimulation (rTMS) and transcranial direct current stimulation (tDCS) [2].

Previous research in our laboratory has shown that approximately 40% of chronic pain patients obtained at least 20% improvement in pain scores following high-frequency rTMS of the M1 motor cortex [3] lasting for approximately 2 weeks consistent with other rTMS studies [4,5]. The effect seems to be maintained as long as rTMS sessions continue, but this requires frequent attendances by patients. The proposed study is based on the hope that tDCS could offer an alternative method for cortical stimulation in this group of patients. As portable tDCS devices have become available, patients/carers can be trained in its application and patients may use these at home without the need for regular visits to our laboratory. If proven sufficiently effective, tDCS could offer an economical and convenient way of delivering cortical stimulation for pain relief.

tDCS involves the application of a low-amplitude constant electric current to the scalp, a proportion of which enters the skull to affect cortical activity in the brain. It does not directly induce action potentials in neurons but rather alters the membrane potential and thus influences the excitability of these cells [6,7]. Typically it is applied via two electrodes, an anode and a cathode, with the current travelling from anode to cathode. The polarity however can be changed by reversing the electrode position. Anodal stimulation of the scalp overlying the cortex results in increased excitability of this cortical area whilst cathodal stimulation has the opposite effect [8].

It has been shown to be effective in the treatment of various conditions including motor function recovery following stroke, reduced epileptiform discharges in epilepsy, mood elevation in depression and improvement of motor function in Parkinson’s disease [9-12].

Several studies have also shown it reduces the perception of acute pain [13,14] and experimentally induced acute pain in healthy volunteers [15,16] and in post-operative pain [17]. In chronic pain conditions that are refractory to medical treatment, anodal tDCS stimulation has been shown to reduce pain (at least in the short term) in fibromyalgia [18,19], pelvic pain [20], cancer pain [21] and spinal cord injury [22,23], although in spinal cord injury pain recent studies have not replicated positive results [24]. In a crossover trial where volunteers were exposed to both anodal and sham tDCS over the M1 motor cortex hand area, Antal et al. [25] demonstrated a reduction in chronic pain scores and a normalisation of intra-cortical inhibition. These effects persist for several weeks after treatment and may reflect long-term plastic changes at neuronal synapses [26-29].

tDCS of the motor cortex also influences the activity of areas distant to the site of stimulation and this is probably achieved through inter-neuronal connections between these sites [30]. This is supported by imaging studies in humans, indicating that cortical stimulation reduces pain by modulating activity in networks of brain areas involved in pain processing, such as the thalamus or by facilitating descending pain inhibitory mechanisms [31-34]. Side effects are uncommon and relatively minor (mostly headache, itch and skin redness) and it is considered a very safe form of treatment with a few contra-indications [35-37].

### Aims

The main aim of this study will be to determine the efficacy of home-based tDCS treatment in two chronic neuropathic pain patient populations: responders and non-responders to rTMS. The hypothesis is that those patients who have previously responded to rTMS will also respond to tDCS while non-responders may not. To test this hypothesis TMS responders will be subjected to three different types of tDCS: anodal, cathodal and sham tDCS. In addition, there remains a possibility that tDCS may show efficacy even in those patients who previously have not responded to rTMS. Therefore, non-responders will be subjected to the same three modes of stimulation as responders.

## Methods/Design

Ethical approval for this study was granted from the National Research Ethics Committee REC reference 12/EE/0315.

### Patient selection

Patients will be selected based on response to previous treatment with rTMS for chronic pain, i.e., all subjects, both responders and non-responders from previous rTMS studies, will be invited to participate. All subjects shall be informed of the purpose of the experiment and written consent to enter the study will be obtained prior to entering the study by the principal investigator.

#### Inclusion criteria

Inclusion criteria include (1) age between 18–85 years; (2) stable analgesic medication for the prior month; (3) mean pain levels ≥4 out 10 on VAS for pain during the 1-week run-in phase, based on patient diary; (4) willingness to take part; (5) ability to consent; (6) previously had a minimum of five sessions of TMS for pain, and can be named as a “responder” or “non-responder” where the responder reports a weekly average pain reduction of 20% on an NRS of 0–10, following five rTMS sessions.

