### Study design

This study will be a randomised, double-blind, double cross-over, sham-controlled trial. Three stimulation modes will be compared: anodal, cathodal and sham stimulation.

Twelve responders and 12 non-responders to rTMS will be randomly assigned to receive anodal, cathodal or sham stimulation as their first treatment session.

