### Statistical analysis

A linear mixed model will be formed with fixed effects of mode of tDCS, treatment sequence, responder group and treatment period, and the random effect as patient (nested in sequence); the model will be first fitted with the pain intensity data. All patients will be included and all pairwise comparisons will be made with the estimated contrast from this model. Secondary continuous outcome measures will be analysed in the same way as the primary endpoint. Baseline covariates will be incorporated as standard fixed effects but the sensitivity of the results to other ways of incorporating baseline information will be assessed [43]. This information will be used to inform future studies. Where required, change in pain scores pre-post each treatment period will be calculated as the difference between pain during run-in baseline and pain over 3 consecutive weeks following tDCS treatment. Analysis will be performed using Stata software (StataCorp, *Stata Statistical Software*, College Station, TX: StataCorp LP). A proportion analysis will also be carried out with patients separated into responders and non-responders and their response rated as positive (pain reduction from run-in baseline of at least 2 units on VAS 0–10, or 30%) and negative (pain relief less) and analysis carried out separately for the three different tDCS treatments.

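### Whether rTMS response predicts tDCS response is tested only by a proportion analysis that cuts both responses; the mixed model has no mode-by-group term and the percentage rTMS reduction is not used

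*Protocol article*

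**What the plan says.** The Aims section states the question: "The hypothesis is that those patients who have previously responded to rTMS will also respond to tDCS while non-responders may not".

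The label comes from Inclusion criteria, item 6, where "the responder reports a weekly average pain reduction of 20" per cent on a 0–10 NRS after five rTMS sessions. The abstract's Methods/design paragraph says "All patients will have previously completed a study of rTMS of the motor cortex and have been designated as responders or non-responders". Study design builds the sample on the label: "Twelve responders and 12 non-responders to rTMS will be randomly assigned".

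Statistical analysis then uses the label in two places:
- **Mixed model on pain intensity.** The listed terms are "fixed effects of mode of tDCS, treatment sequence, responder group and treatment period", with patient nested in sequence as the random effect. No interaction is listed. Baseline covariates are to be added as fixed effects but are not named.
- **Proportion analysis.** Patients are split by rTMS responder status. Their tDCS result is scored positive or negative at 2 units or 30%, separately for each of the three modes.

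The Sample size section illustrates the second analysis with 8/12 against 2/12 and a Fisher p-value. It says that the study is a pilot without a formal power calculation. No stated analysis uses the size of the rTMS reduction.

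**The concern.** Whether rTMS response carries over to tDCS is the distinctive question of this trial, and it rests on 12 patients against 12. Two features of the stated analysis weaken the answer.

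- The mixed model, which keeps pain on its continuous scale and uses the within-patient design, does not test the question, because responder group does not interact with mode.
- The analysis that does address it reduces both variables to two levels. A patient with a 19% rTMS reduction is treated as unlike one with 21% and the same as one with none. The tDCS result is cut in the same way. Because each mode is analysed separately, a group difference under anodal stimulation is also not set against the same patients' sham result.

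At stake are the chance of seeing a graded relation and how useful the result is to the future studies that the article says it should inform.

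**Working it through.** **Step 1. The plan's own figure.** For 8/12 v 2/12 the margins are 10 positives in 24. The upper tail is [C(12,8)·C(12,2) + C(12,9)·C(12,1) + C(12,10)·C(12,0)] / C(24,10) = (32,670 + 2,640 + 66) / 1,961,256 = 0.0180. The groups are equal, so the two-sided value is 2 × 0.0180 = 0.036, as stated. If 8/12 and 2/12 were the true rates, the exact power of this test at 5% would be 61%.

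**Step 2. What the listed mixed model estimates.** Write the expected pain score as mode + sequence + group + period. Within a patient, anodal minus sham removes sequence and group and leaves (anodal effect − sham effect) plus a period difference. This contrast is the same for responders and non-responders by construction. The differential hypothesis needs (anodal − sham in responders) − (anodal − sham in non-responders), which is the mode-by-group term. That term is not listed, so only the proportion analysis remains.

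**Step 3. Information kept by the label.** "approximately 40% of chronic pain patients obtained at least 20% improvement in pain scores" (Background), so take p = 0.4 above the cut. For a normal predictor and a linear relation, the share kept is φ(c)²/[p(1 − p)]. With c = 0.253 and φ(c) = 0.386, this is 0.149/0.24 = 0.62. With p = 0.5 it is 0.159/0.25 = 0.64. Under 12:12 sampling the simulated share is 0.638, so 24 × 0.638 = 15.3: the 24 patients act like about 15.

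**Step 4. Power under a linear relation (two-sided 5%).** Assumptions, none of them from the article: normal rTMS response with the top 40% as responders, 12 sampled from each side, and a normal outcome Y linear in rTMS response with standardised slope ρ. Y stands for the anodal-minus-sham difference in the first two columns. Ranges cover repeated simulations of 4,000 to 20,000 trials.

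| ρ | percentage, continuous Y | label, continuous Y | label, Y cut at median, Fisher |
|---|---|---|---|
| 0.4 | 52–53% | 35–37% | 16% |
| 0.5 | 75% | 54–55% | 27% |
| 0.6 | 91–92% | 72–73% | 41% |

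The middle column is a two-group comparison of the anodal-minus-sham difference. It approximates the missing mode-by-group interaction. The last column approximates the kind of test that the plan does state. Part of its loss comes from the conservatism of Fisher's test, whose simulated type I error is about 2%. At ρ = 0.5, cutting the outcome costs more (54% to 27%) than cutting the moderator (75% to 54%).

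**Step 5. Power if the truth is a step at 20%.** With Y depending only on the label and the same sampling, label v percentage is 46–47% v 31–32% at a difference of 0.8 SD, 65% v 44% at 1.0 SD, and 80–81% v 58% at 1.2 SD. The order reverses.

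**Step 6. Between the two.** For an S-shaped relation centred on the cut with a total rise of 1.2 SD, percentage v label is 40% v 34%, 52% v 54% and 57% v 67% at logistic steepness of 2, 4 and 8 per SD.

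**The case against.** The strongest reply is that the hypothesis is worded in categories, "those patients who have previously responded to rTMS will also respond to tDCS while non-responders may not", and that recruitment follows it. A group comparison tests exactly that, and a slope asks a somewhat different question. This stands: the groups must remain the main comparison. It does not rescue the listed model, which lacks the group-by-mode term that the categorical hypothesis needs.

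A reader might infer that the percentage always gives the better test, or at worst a smaller gain. Steps 5 and 6 show otherwise: under a step it loses, and the article gives no evidence for either shape.

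A reader might also infer that the percentage is on file for every patient. The article says only that patients were designated. It refers to more than one earlier rTMS study, allows more than five sessions, and mentions patients stimulated at several sites. A percentage must once have existed, but one comparable figure per patient is not documented.

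It is fair to add that a pilot without a power claim contradicts nothing by having low power, and that an exploratory moderator model could sit in an unseen analysis plan. However, the article names the model's fixed effects and so fixes the form of this variable. The unnamed baseline covariates, as fixed effects, would not test whether the tDCS effect varies with rTMS response. Finally, a second test of the same question needs a rule for disagreement, and the fix supplies one.

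**Conclusion.** The point holds as a low-cost improvement. As listed, the mixed model cannot answer the differential question, and the analysis that can is cut on both sides. Two separate gains are available.

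- **Interaction on continuous pain scores.** This follows directly from the stated hypothesis and needs no new data. In the linear illustration at ρ = 0.5 it moves power from about 27% to about 54%.
- **Percentage reduction in place of the label.** This would move power from about 55% to 75% in the same setting, but only if the relation is roughly linear. With a step at 20% it would be the weaker test (44% v 65% at 1.0 SD).

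The percentage model therefore belongs beside the groups and should not replace them. The sizes rest on the assumed normal distribution, the 40% share, the assumed slopes and, for the 27%, an outcome cut at the median in place of 2 units or 30%. The two-group powers of about 35%, 55% and 73% should not be read as the power of the plan, because the plan lists no such test. The Fisher p-value of 0.036 is correct.

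**What to change.** In Statistical analysis:

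1. Add a mode-by-responder-group interaction to the mixed model on continuous pain scores, and name its anodal v sham component as the test of the stated hypothesis. Keep the proportion analysis as a descriptive supplement.
2. Pre-specify one supportive model in which the percentage pain reduction after rTMS interacts with mode. Take the percentage from the earlier rTMS study by one fixed rule that says which study, which sessions and which site count.
3. State that the group interaction governs if the two disagree.
4. Plot each patient's anodal-minus-sham difference against rTMS reduction to check linearity.

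This should be fixed before unblinding. The cost is one more model fit, a linearity assumption and one additional supportive test, plus retrieval of the percentages if they are not already in the trial data. If no comparable figure can be recovered for every patient, items 1 and 3 still stand with the group interaction alone.

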#### Exclusion criteria

Exclusion criteria are (1) severe pain of other origin, e.g. musculoskeletal pain that in the opinion of the investigator may interfere with the reporting of the neuropathic pain being targeted; (2) metal implants/coils/electronic devices; (3) drug or alcohol abuse; (4) pregnancy; (5) psychiatric or psychological disorders; (6) epilepsy; (7) inability to understand instructions or operate equipment; (8) high-dose opioids; (9) uncontrolled medical conditions (e.g. active cancer, uncontrolled renal, pulmonary or cardiac disease). (As the patients recruited have passed the stringent rTMS study entry criteria, these restrictions are unlikely to prevent many entering.) Patients were diagnosed with neuropathic pain, according to the new classification [38]. Two specialists (neurologist, pain specialist) had to agree on the diagnosis. Alcohol and drug abuse was ruled out during the interview and review of medical records.

### Study design

This study will be a randomised, double-blind, double cross-over, sham-controlled trial. Three stimulation modes will be compared: anodal, cathodal and sham stimulation.

Twelve responders and 12 non-responders to rTMS will be randomly assigned to receive anodal, cathodal or sham stimulation as their first treatment session.

### Randomisation

Randomisation will be done by a research clerk not otherwise involved in the study. Computer-generated numbers will be used to create the participant numbers and order lists. The latter will be placed in a numbered opaque envelope and sealed. The copy of the order lists and participant numbers is kept by the research clerk.

#### Initial and follow-up assessments

The initial and follow-up assessments will include a record of (1) handedness (not in follow-up assessments); (2) NRS for pain, including measurements for overall daily pain severity, unpleasantness of pain and severity of paroxysmal pain attacks if present. Pain diaries will be filled out daily for 1 week at baseline and for 14 days beginning at each stimulation period [39]. (3) Health status will be assessed by the Short Form 36 Health Survey (SF-36) [39]. (4) Anxiety and depression will be assessed by the hospital anxiety and depression scale (HADS) [40], as well as (5) the mini-mental state examination [41] and (6) patient experience of equipment use, including convenience and adverse effects [39]. Patients are given contact details of medically qualified personnel to contact in case of serious side effects. These will be reported descriptively.

### Determination of the stimulation site

The stimulation site will be the same as used during previous TMS treatments. In practice, this will mean placing the anodal/cathodal electrode over the primary motor or premotor cortex contralateral to the pain. All patients have previously had an MRI of the brain and their localisation on the scalp of the previous TMS treatment can be easily obtained using the brain navigation system associated with the PRI TMS device (eXimia, Nextsim, Helsinki, Finland). In the few cases where this is not possible, the location will be based on bony landmarks as advised by Fregni et al. [10]. In those cases where multiple sites were stimulated using TMS, the site of best response will be chosen.

Direct current will be delivered from a battery-driven, constant current stimulator (Magstim HDCStim stimulator, The Magstim Co., Whitland, UK) using saline-soaked surface sponge electrodes (5 × 5 cm) placed over the previously identified area to target the motor cortex (M1) and over the contralateral supraorbital area. The device will be worn for 20 min each day for 5 days consecutively beginning on the first day of their visit. During active treatment the current delivered will be 1.4 mA with a size 25 cm^2^ electrode. (Changing the direction of the current will result in either anodal or cathodal stimulation with the M1 stimulation being the determinant of which mode is being used.) All subjects are asked to remain non-active during this time and engage in either light reading/watching television or listening to the radio.

### Sham intervention

For sham stimulation, the electrodes are placed in the same positions as for anodal M1 stimulation; however, a constant current of 1.4 mA is only delivered for 30 s (10-s ramp on). During active tDCS treatment, subjects typically report tingling sensations under the electrodes, which rapidly fade [37]. Our sham intervention is therefore designed to provide an initial period of tingling so similar sensations are perceived during active and sham tDCS protocols. This sham protocol has been used by previous investigators [22,42]. Data and instructions on the device display are identical in active and sham settings. Patients will be asked if they can guess the order of stimulation or if they identify any differences in stimulation sessions. This guess will be checked against the actual stimulation order after unblinding.

A research assistant (not otherwise connected with the study) will set the stimulation characteristics as indicated by the information in a sealed envelope opened at the patient visit (anodal/cathodal/sham). This will be repeated at the two subsequent visits. The mode of stimulation is not revealed to the patient or investigators.

